### Interventions

#### The MBTCC group

MBTCC will integrate components from both the MBI and TCC groups, as illustrated in the following. The entire intervention consists of eight weekly sessions of 2.5 to 3 h each. Details are shown in Table 2.

**Table 2 Tab2:** Overview of different interventions

Session	MBI	TCC	MBTCC	SHE
1	● Awareness and automatic pilot ● Mindful eating ● Body and breath meditation	● Learning standing pose ● First posture: beginning Tai Chi ● Second posture: gasp sparrow’s tail	● Approaching mindfulness and TCC ● Mindful standing ● Awareness of breathing ● Practice of the first two postures of TCC	● General introduction of sleep disturbances and sleep hygiene ● Diaphragmatic breathing
2	● Keeping the body in mind ● Body scan ● Sitting meditation	● Standing pose ● First two postures ● Third posture: single whip	● Combining the mind and body together ● Mindful sitting ● Practice of the first three postures of TCC	● Understanding of sleep ● Practice of diaphragmatic breathing
3	● Gathering the scattered mind ● Mindful stretching ● Mindful walking	● Learning twisting pose ● Standing pose ● First three postures ● Fourth posture: lift hand upward	● Joining mindfulness and TCC ● Mindful twisting ● Practice of the first four postures of TCC	● Promoting habits and sleep environment ● Systematic muscular relaxation
4	● Expanding awareness ● Sounds and thoughts meditation ● 3-min breathing space	● Twisting pose ● Standing pose ● First four postures ● Fifth posture: white crane spreads wings	● Awareness expansion ● Mindful walking ● Practice of the first five postures of TCC	● Strengthening bed and bedroom as sleep stimulus ● Practice of systematic muscular relaxation
5	● Allowing/letting be ● Meditation in exploring difficulty ● Breathing space meditation	● Learning walking pose ● Standing pose ● First five postures ● Sixth posture: step forward, deflect, parry, punch	● Living with difficulties ● Learning about accuracy in TCC ● Practice of the first six postures of TCC	● Restricting time in bed ● Imagery rehearsal training
6	● Befriending meditation ● Loving-kindness and compassion ● Cultivating friendship towards oneself	● Walking pose ● Twisting pose ● First six postures ● Seventh posture: like sealing, as if closing	● Self-compassion ● Learning about “song” in TCC ● Practice of the first seven postures of TCC	● Diet relating to sleep ● Practice of imagery rehearsal training
7	● How can I best take care of myself? ● Decision-making in nourishing or depleting	● Standing, walking, or twisting pose ● First seven postures ● Eighth posture: cross hands	● Self-care ● Learning about acceptance in MBI ● Learning about tranquillity in TCC ● Practice of the first eight postures of TCC	● Day time exercises ● Worry containment and management ● Practice of different relaxation methods
8	● Building a precious life ● Weaving mindfulness into daily life	● Standing, walking, or twisting pose ● First eight postures ● Last posture: conclude Tai Chi	● Extending the practice of MBTCC to daily life ● Practice of the whole sets of TCC	● Building up a good and realistic sleep-wake habit ● Relapse management

*MBI* mindfulness-based intervention, *TCC* Tai Chi Chuan, *MBTCC* mindfulness-based Tai Chi Chuan, *SHE* sleep hygiene education

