**Discussion:**

This trial will illuminate the synergetic effect of combining both MBIs and TCC on optimizing improvements in sleep disturbance. The findings from this study can provide empirical support for this integrated treatment, which provides an alternative for healthcare professionals in elderly service to select appropriate practices to treat elderly people with sleep disturbance. It can further help to lessen the growing public health burden of sleep disturbances among the elderly living in the community.

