### Hypotheses

Hypothesis 1. Participants in the MBTCC group will report significantly greater improvements at 8-week (T2), 6-month (T3), and 12-month (T4) follow-ups in regard to measures of the primary outcome of insomnia severity, compared with participants in the MBI-alone group, the TCC-alone group, and the SHE control group.Hypothesis 2. Participants in the MBI-alone group will experience significantly greater improvements than those in the SHE control group in the primary outcomes across time, in which the beneficial effects on insomnia severity will be mediated by rumination and psychological function.Hypothesis 3. Participants in the TCC-alone group will experience significantly greater improvements than those in the SHE control group in the primary outcomes across time, in which the promising effects on insomnia severity will be mediated by the arousal level and physical function.Hypothesis 4. The favourable effects of the MBTCC group on insomnia severity will be mediated by all the proposed mediators.

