#### The MBI group

The MBI group is mainly based on the basic theory and research of the foundational mindfulness-based stress reduction programme [13]. Within this group, participants will cultivate the learning of mindfulness through various kinds of mindfulness activities, such as body scans, sitting meditation, mindful movements, mindful walking, and mindful eating. The intervention consists of eight weekly sessions of two to two-and-a-half hours each. Modifications to the content were carried out, to make it more suitable for elderly people with sleep disturbances. Information sheets about the MBI will be given to the participants. In order to facilitate practice through homework, each participant will be provided with an audio clip, which will be uploaded to their smartphones. All participants will be advised to practise mindfulness meditation at home on a daily basis, using the audio clip, and record it in a logbook.

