#### The TCC group

TCC is mainly based on a nine-form Yang-style form of TCC, which is a brief and modified version of 64-form Yang-style TCC. It can be easily learned and practised without restrictions on time and space. Within the group, participants will be guided through learning the nine sequential forms of TCC movements. In addition, they will learn TCC post-standing, TCC walking, and TCC twisting. The essence of accuracy, “song”, and tranquillity will also be cultivated throughout the sessions. The entire intervention consists of eight weekly sessions of two to two-and-a-half hours each. Information sheets about the principles and skillsets of each form of TCC will be provided to each participant. Video clips will be provided and uploaded to participants’ smartphones to enable home practice. They will be advised to participate in daily home practice and keep a record of their daily practice.

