#### Intervention and assessment fidelity

Each group will be taught by two qualified instructors and each session will be conducted in a similar amount of contact time. Each programme will consist of eight weekly sessions of 2 to 3 h each (16 to 24 h in total). There will be eight to 12 participants in each group. To ensure the fidelity of the intervention, qualified therapists with basic professional training in the teaching of mindfulness-based interventions, in addition to at least 2 years of experience conducting mindfulness-based programmes, will be invited to teach the MBTCC and MBI groups. Experienced Tai Chi masters will be invited to implement the MBTCC and TCC groups. The invited Tai Chi masters should have at least 10 years of experience of practice and teaching TCC. Experienced occupational therapists with at least 10 years of experience conducting mental health psychoeducation programmes will be invited to implement the SHE control group. The fidelity of each intervention programme will be ensured and monitored by a random review of two out of eight sessions. Based on the programme content of the respective intervention programmes, fidelity checks will be independently conducted by an experienced mindfulness instructor, an experienced Tai Chi master, or an experienced occupational therapist. For the qualitative part of the research project, the research personnel will receive half a day of training to learn the corresponding interview questions and the process for conducting the focus groups. In addition, regarding the qualitative analysis, another team of independent raters will audiotape, transcribe, and review the contents of the qualitative interviews to identify corresponding themes.

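### MBTCC sessions are planned at 2.5–3 h and all three comparators at 2–2.5 h, so similar contact time is not assured; an MBTCC advantage could not be credited to integration alone, nor would it show synergy

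*Protocol article*

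**What the plan says.** Session length is given arm by arm under Interventions in the protocol article.

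- MBTCC: "The entire intervention consists of eight weekly sessions of 2.5 to 3 h each".
- MBI: "The intervention consists of eight weekly sessions of two to two-and-a-half hours each".
- TCC: "The entire intervention consists of eight weekly sessions of two to two-and-a-half hours each". The section on the SHE control group gives the same length.

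The section Intervention and assessment fidelity then says of all groups that "each session will be conducted in a similar amount of contact time", and gives one range for every arm: "Each programme will consist of eight weekly sessions of 2 to 3 h each (16 to 24 h in total".

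Hypothesis 1 predicts greater improvement in insomnia severity for MBTCC "compared with participants in the MBI-alone group, the TCC-alone group, and the SHE control group". The Discussion part of the abstract says what the result is meant to show: "This trial will illuminate the synergetic effect of combining both MBIs and TCC on optimizing improvements in sleep disturbance". The Background expects the combination to do better than either method on its own.

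**The concern.** The pooled range of 2 to 3 h hides how the time is divided. Only MBTCC may run beyond 2.5 h, and only the comparators may run below it. The arm that Hypothesis 1 favours is thus never planned to get less contact than a comparator, and in most of the permitted range it gets more.

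Planned contact time is a property of the arm. Randomisation does not balance it, and a covariate for it would be collinear with the arm indicator. The analysis section names age and gender as example covariates, but no choice of covariates or model could separate planned hours from programme content. The primary outcome is the self-reported Insomnia Severity Index (ISI), which more attention and supervised practice could plausibly move.

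The second issue is one of inference. Showing that MBTCC is better than MBI and better than TCC answers whether the package beats each component. It does not answer whether the two methods reinforce each other, which is what synergy means.

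**Working it through.** **1. The plan's own total.** Eight sessions of 2 to 3 h: 8 × 2 = 16 h and 8 × 3 = 24 h. This reproduces the stated 16 to 24 h, but only with all arms pooled.

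**2. The same product by arm.**

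| Arm | Hours per session | Total | Midpoint |
|---|---|---|---|
| MBTCC | 2.5–3 | 20–24 h | 22 h |
| MBI, TCC, SHE (each) | 2–2.5 | 16–20 h | 18 h |

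- Midpoints: 22/18 = 1.22, so 4 h or 22% more for MBTCC.
- Both at the lower limit: 20/16 = 1.25. Both at the upper limit: 24/20 = 1.20.
- Smallest gap: 20 − 20 = 0 h. Largest gap: 24 − 16 = 8 h, and 24/16 = 1.50.

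**3. How much could hours matter?** This is an illustration under two assumptions that the article does not make: the pilot sessions had these lengths, and benefit is proportional to hours. The pilot ISI changes from Table 1 (post minus pre) are:

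- MBTCC: 14.40 − 17.10 = −2.70
- MBI: 15.64 − 17.27 = −1.63
- TCC: 15.70 − 17.22 = −1.52
- SHE: 16.90 − 16.95 = −0.05

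The share of each MBTCC advantage that extra hours would explain is comparator change × (hours ratio − 1) / gap.

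| Comparator | Gap (ISI points) | Ratio 22/18 | Ratio 24/16 |
|---|---|---|---|
| MBI | 1.07 | 1.63 × 0.222 / 1.07 = 34% | 1.63 × 0.5 / 1.07 = 76% |
| TCC | 1.18 | 1.52 × 0.222 / 1.18 = 29% | 1.52 × 0.5 / 1.18 = 64% |
| SHE | 2.65 | 0.05 × 0.222 / 2.65 = 0.4% | 0.05 × 0.5 / 2.65 = 1% |

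The gaps themselves are poorly known. With the post-test SDs, the standard error of the MBTCC–MBI gap is about √(3.10²/10 + 3.44²/22) = 1.2 points.

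**4. Does beating both single arms show synergy?** Let SHE have mean change s, let MBI add m and TCC add t (both negative, meaning benefit), and let the combination give s + m + t + i. Then MBTCC − MBI = t + i and MBTCC − TCC = m + i. With i = 0, meaning no synergy, both differences are still negative and Hypothesis 1 is still met. The quantity that measures synergy is i itself:

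MBTCC − MBI − TCC + SHE = i, where a negative value means more than additive.

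**5. What the pilot says about i.** On changes: −2.70 + 1.63 + 1.52 − 0.05 = +0.40. On post-test means alone: 14.40 − 15.64 − 15.70 + 16.90 = −0.04. Assuming that change scores have SDs close to the post-test SDs, the standard error is √(3.10²/10 + 3.44²/22 + 3.21²/23 + 3.55²/21) = √2.55 ≈ 1.6. The 95% interval for +0.40 is then about −2.7 to +3.5.

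**The case against.** Four counter-arguments deserve a fair hearing.

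*The statements do not strictly contradict each other.* A reader might infer that they cannot all be true. They can: if every arm runs exactly 2.5 h per session, each range is respected and contact time is equal. Similar also does not mean identical, and 2 to 3 h is a correct envelope of the arm ranges. This stands. What remains is that equality holds at one shared endpoint only and nothing in the article fixes delivery there.

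*Extra time is not a full explanation.* A reader might infer that longer sessions could account for the whole MBTCC advantage, or that integration would deserve no credit. The figures do not support that. Under the proportional assumption, hours explain about 29–34% of the gap over the single arms at the midpoints and 64–76% at the extreme, and almost nothing of the gap over SHE. Contact time is a competing explanation, and a real effect of integration is not excluded.

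*The pilot does not speak against synergy.* It is tempting to read +0.40 as less than additive. With 10 MBTCC participants, an interval from about −2.7 to +3.5, and −0.04 on post-test means, that reading fails.

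*No hypothesis claims synergy, and a programme teaching two methods may reasonably run longer.* Both are true. Hypothesis 1 compares packages, and unequal length is a legitimate design choice. But the abstract says what the trial will reveal, and the fidelity section says that contact is similar. A longer package cannot carry both statements.

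**Conclusion.** The concern holds in a limited form. Planned contact is 20–24 h for MBTCC and 16–20 h for each comparator. Any difference favours MBTCC, by 22% at the midpoints and by at most 50%. These figures come directly from the article and need no assumption; the shares of the pilot gaps rest on the two assumptions stated with them.

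The trial remains valid as a comparison of programmes. What is not supported is crediting an MBTCC advantage, chiefly over MBI and TCC, to integration alone. The same caution applies to Hypothesis 4, which concerns how the MBTCC effect arises. MBI versus SHE and TCC versus SHE have equal stated hours, so those contrasts in Hypotheses 2 and 3 are unaffected.

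Independently of session length, success on Hypothesis 1 would not establish synergy, and the pilot data are too imprecise to point in either direction.

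**What to change.** 1. Reconcile the session lengths in the four intervention sections with the similarity statement in the fidelity section. Which length is right is for the clinical team.
2. If a difference is kept, or has already been delivered (recruitment was expected to run from September 2022 to April 2025), remove the similarity statement. Word the Hypothesis 1 conclusion as the longer integrated programme versus the shorter single programmes.
3. Report MBTCC − MBI − TCC + SHE for the primary outcome with its confidence interval, or drop the word synergetic from the conclusions. If session lengths stay unequal, this contrast also carries the extra MBTCC time, and the report should say so.

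The cost is wording, possibly scheduling, and one contrast from a model already planned. The downsides are a narrower claim and an imprecise estimate. With equal arms and SDs, the contrast has a standard error √(4/2) = 1.41 times that of a pairwise comparison. As an illustration from single-time-point means, take 45 completers per arm (180/4) and SDs of 3.10 to 3.55 as in the pilot. The 95% half-width is then 1.96 × SD × √(4/45), or about 1.8 to 2.1 ISI points.

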#### The MBI group

The MBI group is mainly based on the basic theory and research of the foundational mindfulness-based stress reduction programme [13]. Within this group, participants will cultivate the learning of mindfulness through various kinds of mindfulness activities, such as body scans, sitting meditation, mindful movements, mindful walking, and mindful eating. The intervention consists of eight weekly sessions of two to two-and-a-half hours each. Modifications to the content were carried out, to make it more suitable for elderly people with sleep disturbances. Information sheets about the MBI will be given to the participants. In order to facilitate practice through homework, each participant will be provided with an audio clip, which will be uploaded to their smartphones. All participants will be advised to practise mindfulness meditation at home on a daily basis, using the audio clip, and record it in a logbook.

#### The TCC group

TCC is mainly based on a nine-form Yang-style form of TCC, which is a brief and modified version of 64-form Yang-style TCC. It can be easily learned and practised without restrictions on time and space. Within the group, participants will be guided through learning the nine sequential forms of TCC movements. In addition, they will learn TCC post-standing, TCC walking, and TCC twisting. The essence of accuracy, “song”, and tranquillity will also be cultivated throughout the sessions. The entire intervention consists of eight weekly sessions of two to two-and-a-half hours each. Information sheets about the principles and skillsets of each form of TCC will be provided to each participant. Video clips will be provided and uploaded to participants’ smartphones to enable home practice. They will be advised to participate in daily home practice and keep a record of their daily practice.

#### The SHE control group

SHE is based on principles used in stimulus control and sleep hygiene education, which has previously been used as the control group in sleep-related research [20]. General guidelines include (a) go to bed only when sleepy at night; (b) get out of bed and leave the bedroom when unable to fall asleep or go back to sleep within 15–20 min and return to bed only when sleepy again; (c) do not use the bed/bedroom for activities (e.g. watching television, listening to the radio, eating, or reading in bed) other than sleep and sexual activities; (d) get up at the same time every morning; (e) do not nap during the day; and (f) do not compensate for lost sleep during holidays. Other information on the effects of external stimuli, such as environment and relevant relaxation techniques, will also be given and taught to participants. The entire intervention consists of eight weekly sessions of two to two-and-a-half hours each. They will be advised to follow the taught guidelines on a daily basis and keep a record.

#### Intervention and assessment fidelity

Each group will be taught by two qualified instructors and each session will be conducted in a similar amount of contact time. Each programme will consist of eight weekly sessions of 2 to 3 h each (16 to 24 h in total). There will be eight to 12 participants in each group. To ensure the fidelity of the intervention, qualified therapists with basic professional training in the teaching of mindfulness-based interventions, in addition to at least 2 years of experience conducting mindfulness-based programmes, will be invited to teach the MBTCC and MBI groups. Experienced Tai Chi masters will be invited to implement the MBTCC and TCC groups. The invited Tai Chi masters should have at least 10 years of experience of practice and teaching TCC. Experienced occupational therapists with at least 10 years of experience conducting mental health psychoeducation programmes will be invited to implement the SHE control group. The fidelity of each intervention programme will be ensured and monitored by a random review of two out of eight sessions. Based on the programme content of the respective intervention programmes, fidelity checks will be independently conducted by an experienced mindfulness instructor, an experienced Tai Chi master, or an experienced occupational therapist. For the qualitative part of the research project, the research personnel will receive half a day of training to learn the corresponding interview questions and the process for conducting the focus groups. In addition, regarding the qualitative analysis, another team of independent raters will audiotape, transcribe, and review the contents of the qualitative interviews to identify corresponding themes.

### Measurements

The psychometric attributes of all the measurement tools used in this project, such as reliability and validity, are psychometrically sound. For those assessments without a Chinese version, translation and cultural adaptation will be carried out. Outcome assessments will take place at T1 to T4 (i.e. T1, baseline; T2, after the 8-week intervention; T3, 6 months after intervention; T4, 12 months after intervention). All participants will be assessed in terms of the following aspects.

#### Screening measure

Sleep quality will be assessed by the Chinese version of the Pittsburgh Sleep Quality Index [19]. The index consists of a 19-item questionnaire evaluating sleep quality and disturbances over the past month. The first four items are open questions, whereas items 5 to 19 are rated on a 4-point Likert scale. Individual item scores yield seven components. A total score, ranging from 0 to 21, is obtained by adding together the seven component scores. A score higher than 5 suggests poor sleep quality.

#### Primary outcome measures

Insomnia severity will be assessed by the Insomnia Severity Index [21], which is a seven-item self-report questionnaire assessing the nature, severity, and impact of both nighttime and daytime symptoms of insomnia over the past week. It has been validated as a reliable and valid instrument that can be used to detect cases of insomnia in the population and is sensitive to treatment responses in clinical patients. A higher score represents greater insomnia severity. A minimally important treatment response can be indicated by a total score reduction > 7 points, while remission can be denoted by a total score of < 8 [21].

#### Secondary outcome measures

Interoception will be assessed by the Multidimensional Assessment of Interoceptive Awareness Scale [22]. The scale consists of 32 items that can capture changes in interoception associated with mind-body interventions. It comprises eight subscales, including noticing, not-distracting, not-worrying, attention regulation, emotional awareness, self-regulation, body listening, and trusting. A higher score indicates higher levels of interoceptive awareness.

The sleep-wake pattern will be assessed through wrist actigraphy. Wrist ActiGraph GT9X (ActiGraph, Pensacola, USA) will be used to measure sleep-wake patterns. Participants will be asked to put on an easy-to-wear device on the wrist of the non-dominant hand for 1 week at each measurement time period. Data will be collected continuously and stored in 1-min epochs. The sleep-wake pattern will be processed and analysed using ActiLife (V 6.11.9, Pensacola, USA).

